### Randomization

A randomization module with participants stratified into 2 levels (recent suicidality vs no recent suicidality) and randomized into 3 conditions (Caring Contacts with EMA, Caring Contacts alone, and EMA alone) was built into REDCap. Recent suicidality is indicated by a participant endorsing that they have either wished they were dead or had thoughts of killing themself sometime in the past year. This module is programmed to randomize participants with no involvement of study staff to prevent potential bias, with intervention and control assignments distributed evenly across participants. Once participants have completed the online baseline survey, they are randomized into 1 of the 3 conditions (Table 1; Figures 1 and 2). Further details on the EMA procedures are provided in subsequent sections.

**Table 1 table1:** Assessment and intervention message timeline^a^.

Study procedure		Study condition		
		CC^b^ and monthly EMA	CC only	Monthly EMA only
Consent and baseline survey		✓	✓	✓
Two weeks of baseline EMA^c^		✓	✓	✓

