#### Analysis Plan

First, descriptive statistics will be calculated for all variables and group differences in baseline variables will be examined to ensure randomization success. All outcome variables will be examined for nonnormality, and given past suicide research, we anticipate a positive skew for suicidal thoughts and behaviors, and we will use an appropriate model for all analyses based on the distribution of the outcome variables. On the basis of a Directed Acyclic Graph model generated using DAGitty [124,125], demographic variables are conditionally independent of our outcome variables after accounting for the variables specified in our aims and thus do not confound the relationship between the Caring Contacts intervention and our outcome variables. However, to understand the nuanced effects of Caring Contacts on suicide risk across diverse subgroups, we will control for ethnicity, gender, and military status (veteran vs current US military service member) as covariates in our analysis. This stratification allows us to discern potentially differential impacts of the intervention and ensures that our findings are robust and applicable across the varying demographic profiles within the veteran population. Furthermore, all analyses will be conducted using an intent-to-treat framework, using all available data, and using robust maximum likelihood estimation to account for missing data.

For aim 1.1, individual participant means and SDs of each suicide indicator (motivation to live, passive ideation, active ideation, suicide intent, and urges to harm self) will be calculated from the baseline and 12-month EMA period (for all conditions). Then, to assess group differences in the outcome measures of interest, an analysis of covariance examining condition-specific differences at 12 months, controlling for baseline values of the outcome variable of interest, will be conducted. Preplanned post hoc comparisons will compare (1) any Caring Contacts (combined) to no Caring Contacts, (2) Caring Contacts with and without EMA, and (3) EMA with and without Caring Contacts.

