## Discussion

### Significance

This innovative trial will be the first RCT to examine (1) the impact of the Caring Contacts intervention on a broad population experiencing stress or distress and (2) the mechanisms of Caring Contacts, both when each message is received and during the course of the 1-year intervention. By recruiting veterans and service members experiencing a wide variety of stressors and psychological distress, the sample is more generalizable to those served by veteran service organizations, primary care, and general behavioral health care. If Caring Contacts reduces the risk of suicide, improves psychological distress, or both, then the intervention could be scaled up to include individuals who do not endorse suicidality but have the potential to benefit. As veteran service organizations are not equipped to systematically assess suicidality or to provide an intervention specifically for this segment of their membership, positive results would support their implementation with any veteran experiencing stress or distress.

EMA provides a powerful tool for measuring the impact of Caring Contacts by enabling real-time data collection in participants’ natural environments. This approach minimizes recall bias and allows a detailed exploration of how the intervention affects participants immediately after receiving Caring Contacts and over the course of 1 year. Thus, EMA allows researchers to gain valuable insights into the mechanisms of action of the Caring Contacts intervention. This can address critical gaps in understanding and pave the way for improved, scalable strategies to prevent suicide.

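### Covariate adjustment cannot show differential impacts as the plan claims, and the randomization stratum is in no planned model although one conclusion concerns people without suicidality

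*Protocol article*

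**What the plan says.** Data Analysis, Analysis Plan: after explaining that demographic variables are not expected to confound the treatment effect, the article says that "we will control for ethnicity, gender, and military status (veteran vs current US military service member) as covariates in our analysis". The stated purpose is "to understand the nuanced effects of Caring Contacts on suicide risk across diverse subgroups", and the next sentence claims "This stratification allows us to discern potentially differential impacts of the intervention".

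The model for aim 1.1 is "an analysis of covariance examining condition-specific differences at 12 months, controlling for baseline values of the outcome variable of interest, will be conducted"; aims 1.2 and 3 use the same form. The preplanned comparisons are "any Caring Contacts (combined) to no Caring Contacts, (2) Caring Contacts with and without EMA, and (3) EMA with and without Caring Contacts". Baseline variables found to be imbalanced are to be added as covariates for aims 1.1 and 1.2.

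Methods, Randomization: participants are "stratified into 2 levels (recent suicidality vs no recent suicidality) and randomized into 3 conditions". The stratum is a wish to be dead or thoughts of killing oneself in the past year.

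Discussion, Significance: if Caring Contacts reduces suicide risk, improves distress, or both, "then the intervention could be scaled up to include individuals who do not endorse suicidality but have the potential to benefit".

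**The concern.** There are two linked problems.

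First, a named method is credited with an inference it cannot give. A covariate without a product term shifts the outcome level between groups and leaves the treatment effect identical in all of them. The text also rules out confounding as the reason for including these three variables, so the reason it gives rests largely on a subgroup purpose they cannot serve in this form.

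Second, the modifier closest to the trial's motivation is past-year suicidality. The investigators thought it important enough to stratify on, yet no described model, contrast or subgroup estimate uses it. The sample is mixed by design, because suicidal ideation and suicide cognitions are among the qualifying markers in Eligibility Criteria. A positive pooled result could therefore be read as evidence for people without suicidality when the analysis has not looked at them separately.

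**Working it through.** **1. The plan's nearest figure.** The differential-impact claim rests on no number. The closest is the detectable effect for aim 1.2 in Power and Sample Size, f²=0.03 with N=510, α=0.05 and power 0.95. With a noncentral F for three groups (numerator df 2, denominator df 507, noncentrality 510×f²), power 0.95 is reached at f²=0.0305, which agrees. That figure concerns the overall comparison of conditions and says nothing about effect differences between groups.

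**2. What the covariate model can return.** The model is 12-month outcome = intercept + condition + baseline value + group. The condition coefficient is one number, averaged over groups. In 1,000 simulated trials (340 vs 170, two groups of about half the sample, true effects 0 and 0.8), the covariate model gave a single mean effect of 0.39, close to 0.5×0 + 0.5×0.8 = 0.40, and nothing about the difference. Adding condition × group detected the difference in 98.8% of runs.

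**3. Whether suicidality enters elsewhere.** The Analysis Plan describes ANCOVAs on condition and baseline outcome, three between-condition contrasts, an exploratory growth model with condition on intercept and slope, and a within-person mediation model. None contains the stratum. The rule for imbalanced baseline variables is unlikely to bring it in, because stratified randomization balances it, and would add only a main effect.

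**4. What a pooled effect leaves open.** Let q be the share with recent suicidality. The pooled effect is about q×d₁ + (1−q)×d₀. Take 0.34, the effect detectable with 95% power for any Caring Contacts versus none: 3.605×√(1/340+1/170) = 3.605×0.0939 = 0.339. At q=0.50 this fits 0.34 in both strata, or 0.34/0.50 = 0.68 and 0. With no effect in the other stratum, q=0.25 requires 0.34/0.25 = 1.36, and q=0.139 requires 0.34/0.139, about 2.4.

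**5. Precision of the stratum analyses.** Inputs: 510 participants allocated evenly (Randomization), so 340 any Caring Contacts and 170 none. q is not stated, so a range is shown. The documents' 13.9% (71/510) is expected current ideation, not the past-year stratum, and serves here only as one end of the range.

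- SE of the pooled contrast: √(1/340+1/170) = 0.0939 SD.
- Interaction detectable with 80% power: 2.80×0.0939/√(q(1−q)).
- Effect in the no-recent-suicidality stratum: 95% CI half-width 1.96×0.0939/√(1−q); detectable with 80% power at 2.80×0.0939/√(1−q).

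| q | Interaction d | n without recent suicidality | 95% CI half-width | Detectable d in that stratum |
|---|---|---|---|---|
| 0.139 | 0.76 | 439 | ±0.20 | 0.28 |
| 0.25 | 0.61 | 382 | ±0.21 | 0.30 |
| 0.50 | 0.53 | 255 | ±0.26 | 0.37 |
| 0.75 | 0.61 | 128 | ±0.37 | 0.53 |
| 0.861 | 0.76 | 71 | ±0.49 | 0.71 |

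The pooled contrast is detectable with 80% power at 2.80×0.0939 = 0.26, so the interaction needs a difference 2.0 to 2.9 times as large. Baseline adjustment would narrow these figures (at an assumed baseline correlation of 0.6, by a factor √(1−0.36) = 0.8); attrition would widen them.

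**The case against.** The strongest reply is that the sentence in the Analysis Plan concerns ethnicity, gender and military status only. It promises nothing about suicidality, and subgroup terms are often left to a statistical analysis plan that is not shown. That is fair as far as it goes: a missing subgroup analysis in a condensed article would not be a finding. It does not rescue the sentence, because the article itself names the method and the inference, and the method cannot deliver it whatever another document adds. For suicidality, the point rests on the Discussion drawing a conclusion that the analyses described do not address, not on the omission alone.

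A second reply is that the pooled effect is the relevant quantity. The Objective and Conclusions in the Abstract describe people recruited for stress or distress and not on the basis of suicidality, and the Discussion argues from veteran service organizations that cannot screen systematically. This stands. A reader might infer that the trial cannot support or refute its headline conclusion; the documents do not support that. Only the clause about people who do not endorse suicidality outruns the planned analysis, and that clause is worded conditionally.

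A reader might also infer that participants without recent suicidality sit at the floor of the primary items. No distribution by stratum is given. The Analysis Plan expects positive skew in general, and one of the three items is reverse-coded motivation to live, which need not be at its floor in distressed people.

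Finally, whether a pooled effect could plausibly arise from one stratum alone depends on the split. At 50:50 the required 0.68 is conceivable; at 13.9% the required 2.4 is not.

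**Conclusion.** The differential-impact claim is wrong as written, and this needs no assumption: main-effect covariates fit one common effect, and no product term or subgroup estimate is described.

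The suicidality part holds in a narrower form. The randomization stratum is absent from every described model, so the pooled effect cannot on its own support extension to people who do not endorse suicidality, although it does answer the question for the mixed population. The primary estimates themselves are not invalidated.

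The precision figures assume full N, even allocation, no baseline adjustment and an unstated stratum split. Under any split in the range, the interaction is much harder to detect than the main effect, so stratum results can inform the conclusion but not confirm it. This should be corrected; it is not a fatal flaw.

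**What to change.** 1. Delete the claim that covariate adjustment discerns differential impacts, or replace it with condition-by-covariate terms for ethnicity, gender and military status, labelled exploratory.
2. Include the randomization stratum in the aim 1.1 and 1.2 ANCOVAs.
3. Report the any-Caring-Contacts versus none effect with a 95% CI in each suicidality stratum, and the condition-by-stratum interaction as an estimate with its CI.
4. Word the extension in the Discussion in light of the no-recent-suicidality estimate and its CI, without making it a pass/fail rule on one imprecise estimate.

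The cost is one sentence and a few model terms on data already being collected. The article places analysis after data collection, so the terms can still be fixed in advance. The downsides are low precision, as tabulated, and multiplicity: four modifiers across the three EMA items and two survey scales would be 4×5 = 20 interactions. Deleting the claim instead of adding the demographic terms leaves five, all for the stratum. In either case the results should be labelled as not confirmatory.

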#### Informed Consent

The informed consent process was designed to be interactive within the REDCap (Research Electronic Data Capture; Vanderbilt University) secure online environment. To facilitate the informed consent process, participants are presented with a video that walks them through the study procedures. REDCap prevents participants from advancing to the next page for the first 3 minutes to encourage participants to engage with the video (which is just over 7 minutes long). They then proceed to the next page, where they can review the consent document in its entirety (provided in Multimedia Appendix 2). To ensure complete understanding, participants are asked 10 true or false questions about the study procedures, payment structure, and safety measures that are in place. The REDCap page allows 2 chances to answer each question correctly, and only those participants who answered correctly are asked whether they want to participate in the study. Throughout this process, participants are reminded that study staff are available by request to clarify all informed consent documents and study procedures via telephone or videoconference. They are also reminded that at any time they can (1) refuse to complete any or all the surveys and EMAs, (2) decline the qualitative interview, (3) opt out of receiving the intervention messages, or (4) withdraw from the study entirely.

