Participants are free at any time to request that they stop receiving Caring Contact messages. In such cases, study staff will inquire if they are willing to continue with the other parts of the study (EMA, the follow-up survey, and the qualitative interview), and each participant is able to decide at what level they will proceed. Participants may also ask for the messages to be paused for a certain period (eg, if they are traveling or otherwise unable to be contacted), in which case the study team will simply remove any messages scheduled to be sent during the specified period. As described in subsequent sections, the web-based platform used to deliver the Caring Contacts intervention is able to track the number of messages to and from each participant, so it will be evident during data analysis how many intervention messages each participant received. Requests to temporarily pause the messages will not change the overall length of the intervention.

We do not anticipate any reasons to withdraw participants from the intervention. However, if withdrawal is considered, the principal investigator, coinvestigators, and lead research scientists will consult together (with the UW IRB and the study DSMB as appropriate) to determine why such a decision is in the best interest of the participant and only withdraw them for that reason. In the case of a withdrawal, the principal investigator will contact the participant via email to explain the withdrawal and reasons for doing so and include an offer of a meeting to discuss further should the participant desire it.

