#### EMA Study

Participants will receive invite links to complete the EMAs at various time points across the study period, as shown in Table 1. Each EMA point has 10 or 11 items (described in the subsequent section), which usually take 30 seconds to 3 minutes to complete (based on participants enrolled thus far and the pilot testing of the EMAs). All participants will initially receive invitations for 3 daily assessments for 14 days before randomization (42 assessments) to establish baseline mean and variability metrics for the EMA outcomes and mechanisms, and an additional 7 days of EMA (21 assessments) at 12-month follow-up. Participants randomized to conditions that include EMA, following the baseline assessment period, complete 7 days of EMA per month at months 1 to 11 (231 assessments) to assess real-time mean and variability of risk and potential mechanisms (Table 1).

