For those participants who will complete EMA for all 12 months (n=340), we will conduct an *exploratory analysis* of changes over time in the mean and intraindividual SD of suicide outcomes. The unique and intensive sampling approach of EMA allows for fine-grained exploration of if and when outcomes change in a clinical trial. Specifically, we will first visually examine trajectories by condition to determine the shape of change *trajectories* over time. Then, following the determination of the shape, we will conduct a linear mixed effects growth model (eg, linear, nonlinear quadratic, and piecewise) [126-129], including a dummy-coded condition variable (with EMA only as the reference) as a predictor of both intercept and slope to determine how intervention condition impacts change in suicide outcomes over time.

For aims 1.2 and 3, to examine secondary suicide outcomes and measures of psychological distress, we will use analysis of covariance to examine condition-specific differences in continuous scores of suicide ideation and cognitions and examine group differences at 12 months, controlling for baseline values of the outcome variable of interest. Similarly, preplanned post hoc comparisons will compare (1) any Caring Contacts (combined) to no Caring Contacts, (2) Caring Contacts with and without EMA, and (3) EMA with and without Caring Contacts. For both aims 1.1 and 1.2, any baseline variables that were not successfully randomized will be included as covariates in the regression models.

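### Aim 1.1: maximum likelihood on a single month-12 outcome does not account for missing month-12 EMA, so the ANCOVA is in effect complete-case for missing outcomes

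*Protocol article*

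**What the plan says.** All references are to the protocol article.

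- **Missing data.** The Analysis Plan states for every aim that "all analyses will be conducted using an intent-to-treat framework, using all available data, and using robust maximum likelihood estimation to account for missing data".
- **Aim 1.1 model.** The same section computes each participant's mean and SD from the baseline and 12-month EMA periods, then applies "an analysis of covariance examining condition-specific differences at 12 months, controlling for baseline values of the outcome variable of interest". Ethnicity, gender and military status are covariates, as are any imbalanced baseline variables.
- **Outcome window.** The EMA Study section gives every arm "an additional 7 days of EMA (21 assessments) at 12-month follow-up". Months 1-11 EMA (231 assessments) exists only in the two EMA arms.
- **Use of months 1-11.** An exploratory growth model is introduced with "For those participants who will complete EMA for all 12 months (n=340), we will conduct an". The aim 4 models also use EMA data from within the EMA periods. The aim 1.1 ANCOVA does not use months 1-11.
- **Non-response is foreseen.** Under Informed Consent, participants may "refuse to complete any or all the surveys and EMAs". Under Caring Contacts Intervention, those who stop the messages are asked whether they will continue the other parts, and "each participant is able to decide at what level they will proceed".

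**The concern.** The sentence on maximum likelihood reads as the plan's answer to missing data, including missing primary outcomes. Likelihood methods recover information on a missing outcome only through other variables in the model that were observed after randomization. The aim 1.1 ANCOVA contains none. The stated remedy and the stated model therefore do not fit together.

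At stake is the primary EMA comparison. If participants who fare badly during the year are less likely to answer in month 12, and this shifts the observed means by different amounts in different arms, the condition effect is biased. Neither the baseline value nor the maximum-likelihood statement removes that bias. Precision is also lost, although related data will have been collected: follow-up survey scores in all arms and interim EMA in two.

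**Working it through.** **1. The plan's own power figures.** Inputs from Power and Sample Size: N = 510, three conditions, α = 0.05, power 0.95. Use the noncentral F test with u = 2, v = N − 3 and λ = f²(u + v + 1) = f²N. Solving at N = 510 gives f² = 0.0305, that is f = √0.0305 = 0.1745. The aim 1.2 figure (f² = 0.03) reproduces, with power 94.7%. The aim 1.1 figure of 0.17 does not reproduce as f² but matches f. That labelling matter is separate and does not affect this point. Both figures assume that all 510 are analysed. If only those with an outcome count, by assumed loss:

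| Loss | N analysed | Detectable f² (95% power) | Power at f² = 0.03 |
|---|---|---|---|
| 0% | 510 | 0.0305 | 94.7% |
| 10% | 459 | 0.034 | 92.2% |
| 20% | 408 | 0.038 | 88.7% |
| 30% | 357 | 0.044 | 83.9% |

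**2. Why maximum likelihood adds nothing here.** Write B for baseline, Y for the month-12 summary and X for arm and covariates. One person's likelihood is f(B | X) × f(Y | X, B). If Y is missing, the second factor integrates to 1, so that person informs only the baseline distribution and not the arm coefficient. Check: 200 simulated trials of N = 510 with about 26% of Y missing. The condition effects from maximum likelihood and from complete-case ANCOVA agreed to within 6 × 10⁻¹² in every trial.

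**3. What an auxiliary variable changes.** Add A, observed after randomization. The arm effect on Y is then γ_arm + γ_A × δ_arm. Here the γ terms come from regressing Y on arm, B and A among those with Y, and δ_arm comes from regressing A on arm and B among everyone with A. People without Y now contribute through δ_arm.

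**4. Who is lost.** One answered prompt gives a mean and two give an SD. For the mean outcome, only those answering 0 of 21 are lost. No rate is stated for this. The 50% completion figure in the article is a stress test in the aim 3 power calculation. Taking it as an assumed average, a beta-binomial gives the share with 0 of 21 as about 0% if all respond alike, about 5% if individual response rates are uniform (1/22 = 0.045), and 12% if they are U-shaped (Beta(0.5, 0.5)). Outright dropout would add to this.

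**5. Could response differ by arm?** From Table 1 and Payment Structure, the Caring-Contacts-only arm has 2 + 1 = 3 assigned EMA weeks and each EMA arm has 2 + 12 = 14. The stated maxima confirm this: 25 + 3×10 + 50 + 25 + 50 = 180 and 25 + 14×10 + 50 + 25 + 50 = 290 (US $). The $50 bonus needs 80% of assigned weeks. With month 12 skipped, the attainable share is 2/3 = 67% in the Caring-Contacts-only arm (bonus lost) and 13/14 = 93% in the EMA arms (bonus kept). The incentive to answer in the outcome week thus differs by arm, which bears on contrasts (1) and (2). In contrast (3) the EMA schedule is the same, and only one of the two arms gets personal messages.

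**6. Size of bias under assumptions.** Simulated contrast (3): 170 v 170, no true effect, baseline-to-month-11 correlation 0.6, month-11-to-12 correlation 0.7 to 0.85. Slopes are log-odds of non-response per SD of the month-11 score.

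| Missing | Slope, EMA only | Slope, Caring Contacts + EMA | ANCOVA bias (SD) | Rejection at nominal 5% |
|---|---|---|---|---|
| 25% | 0.6 | 0 | 0.07-0.08 | up to about 11% |
| 25% | 0.6 | 0.3 | 0.03-0.04 | about 6% |
| 12% | 0.6 | 0 | 0.03-0.04 | about 6% |
| 5% | 0.6 | 0 | about 0.015 | 5-6% |
| any | equal | equal | none | not inflated |

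In the first row, joint maximum likelihood with the interim score was unbiased (0.000 and 0.002). With loss completely at random it cut the variance by 9 to 15%. Exact values shift with details of the simulated model, so read them as orders of magnitude.

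The simulation in step 2 had non-response driven by interim EMA with a common slope in the two EMA arms. There, contrast (3) averaged −0.271 by ANCOVA, −0.286 with interim EMA as auxiliary, and −0.283 with full data, so little was at stake.

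**The case against.** **The analysis plan is not shown.** Auxiliary variables and missing-data sensitivity analyses are often left to it, and nothing in the article excludes them. A reader might infer that the trial cannot use these participants at all, which the documents do not support: the same likelihood fit with auxiliaries could use them. What stands is narrower. The article names the model, its two data windows and the missing-data method, and as named the method does nothing for missing outcomes.

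**ANCOVA on observed outcomes is conventional.** It is valid if response depends only on arm, baseline and covariates. That is correct, and bias is conditional, not established.

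**Retention is addressed.** There are weekly payments, the bonus, backup contacts, and a 6-month check for participants who have gone silent. These should reduce loss, although the bonus works differently by arm (step 5).

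**The larger bias figures rest on a chosen scenario.** That is so. Neither the 25% loss nor the one-arm slope is in the article, and milder inputs give 0.04 SD or less.

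**A repeated-measures model over months 1-11 is not plainly better as primary.** One arm lacks those months by design, its covariance would be borrowed from arms whose monthly EMA may itself affect outcomes, and the 0-10 items are expected to be skewed. This stands, and it is why the fix does not replace the primary contrasts with such a model.

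**Conclusion.** The point holds in this form: for participants with no month-12 EMA response, the maximum-likelihood statement adds nothing to the aim 1.1 condition effect, and the ANCOVA is complete-case in that respect. This follows from the model as written and needs no assumed rate.

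The size of any bias is unknown, because no attrition rate is given for aim 1.1. Under the assumptions above it runs from none to about 0.07 to 0.08 SD, the upper end needing 25% loss and strongly differential response. Precision loss is moderate: at 20% loss, power at f² = 0.03 falls from 94.7% to 88.7%.

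Three stronger readings are tempting but not supported.

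- *Everyone who stops EMA is lost.* A single answered month-12 prompt gives a mean.
- *Intent-to-treat is abandoned.* Analysis by assigned arm is kept. What fails is the inclusion of all randomized participants. Maximum likelihood can also retain people with a missing baseline value if baseline is modelled jointly.
- *Months 1-11 serve only the exploratory growth model.* The aim 4 models use the EMA data too. Those months are absent only from the aim 1.1 ANCOVA.

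**What to change.** - **Primary.** Keep the baseline-adjusted month-12 condition contrasts. Fit them by full-information maximum likelihood, with the follow-up HASS suicidal ideation and Brief Suicide Cognitions Scale scores as auxiliary variables. Both are collected in all three arms, and the survey window stays open for 3 months with reminders, so some people who miss the EMA week should still have them.
- **Sensitivity.** Mainly for contrast (3), add the months 1-11 EMA means as auxiliaries or in a joint repeated-measures model.
- **Label.** Report the ANCOVA without auxiliaries as a complete-case sensitivity analysis, and give the number with no month-12 response by arm.

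The cost is somewhat more modelling and text, with no new data. Because the article places analysis after data collection, this can be specified beforehand. The method assumes missingness at random given the added variables. The Caring-Contacts-only arm gains only from the survey scores. The gain depends on how many EMA non-responders return the survey and how closely its scores track the EMA items. The simulations above tested interim EMA as the auxiliary, so they do not measure that gain.

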#### Primary Outcomes (Aims 1.1 and 1.2)

The primary EMA outcomes are mean levels of 3 suicide risk indicators of motivation to live, desire to die, and urges for suicide rated on a Likert scale from 0 to 10 (aim 1.1). The specific items include “How much do you want to die right now?,” “How much do you want to live right now?,” and “How strong are your urges for killing yourself right now?” Higher scores indicate higher suicidal risk (the item regarding motivation to live is reverse-coded). They are assessed at every EMA point throughout the study follow-up period. In the pilot trial of this study, we used visual analog scale (VAS), consisting of a slider on a straight line with end points representing the extremes, to measure these items. Their convenience and ease of rapid administration make them highly compatible with EMA research designs, facilitating efficient real-time data collection in naturalistic settings [59]. VAS of suicide intent [60], suicide desire [61], suicide urges, and perceived burdensomeness [62] were pilot-tested. However, VAS was not found to be user-friendly due to the limitations of the REDCap survey interface when presented on a smartphone. As such, we changed the response options for these suicide risk items to buttons labeled 0 through 10 in place of a VAS from 0 to 100.

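### Aim 1.1 appears to test within-person SDs of 0–10 items with no allowance for level, so a downward shift near 0 can pass for reduced variability

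*Protocol article*

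**What the plan says.** - **Primary Outcomes (Aims 1.1 and 1.2):** "The primary EMA outcomes are mean levels of 3 suicide risk indicators". The items are scored 0 to 10, and "Higher scores indicate higher suicidal risk (the item regarding motivation to live is reverse-coded", so low risk sits at 0. The SD is not named as a primary outcome.
- **Analysis Plan, aim 1.1:** the summaries to be calculated are "individual participant means and SDs of each suicide indicator". The next step is "an analysis of covariance examining condition-specific differences at 12 months, controlling for baseline values of the outcome variable of interest, will be conducted". The mean and the SD are not separated, and the level is not listed as a covariate for the SD.
- **Analysis Plan, exploratory growth models:** these examine "changes over time in the mean and intraindividual SD of suicide outcomes" in the two arms with monthly EMA.
- **Analysis Plan, opening paragraph:** on the expected shape of the data it says "we anticipate a positive skew for suicidal thoughts and behaviors". The choice of model is left open there, to be settled by how each outcome turns out to be distributed.
- **EMA Study:** the baseline period has 42 prompts over 14 days and the 12-month period 21 over 7 days. Measuring variability is one stated purpose of the EMA.

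**The concern.** A within-person SD on a bounded scale is not a measure of variability that is free of level. As a person's ratings approach 0 they have less room to vary, and the SD shrinks even if the underlying fluctuation has not changed. An ANCOVA of the 12-month SD on the baseline SD and arm does not remove this, because a difference in level that arises after randomisation carries straight into the 12-month SD.

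At stake is the interpretation of a secondary message. The trial could report that Caring Contacts stabilises suicidal thinking when the messages only lowered its level. The article presents the study of variability as one of the strengths of EMA, so such a report is foreseeable.

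**Working it through.** The plan gives no figure for the SD analysis, so there is nothing of its own to reproduce. The check is whether a change in level alone can move the SD.

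**Inputs from the article:** 0–10 items; 42 baseline and 21 follow-up prompts; N=510 in three arms, so 170 per arm if split evenly and 340 versus 170 for any Caring Contacts against none; two-sided α=.05.

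**Assumptions not in the article:** a latent normal rating, rounded and clipped to 0–10; latent within-person SD 1.5, the same in both arms; person-level baseline-to-follow-up correlation 0.7; 60% or 70% prompt completion; various distributions of latent person means.

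**Step 1: observed SD at a fixed latent SD of 1.5.** For latent mean m, P(rating = k) = Φ((k + 0.5 − m)/1.5) − Φ((k − 0.5 − m)/1.5), with the lower tail added to 0 and the upper tail to 10. The SD of that distribution is:

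| Latent mean | 5 | 3 | 2 | 1 | 0 | −1 | −3 |
|---|---|---|---|---|---|---|---|
| Observed SD | 1.53 | 1.50 | 1.42 | 1.22 | 0.91 | 0.56 | 0.12 |

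The SD is nearly flat from about 3 to 7 and falls towards either end. Moving from latent mean 1 to 0 cuts it by 1.22 − 0.91 = 0.31 with no change in latent variability.

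**Step 2: simulated trials, ANCOVA of follow-up SD on arm and baseline SD.** Only the level differs between arms; 400 trials per setting.

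| Setting | No shift | 0.5-point drop | 1-point drop |
|---|---|---|---|
| 170 v 170, 60% completion, latent means N(−2, 3), N(0, 3) or N(2, 2.5) | 5–6% | 32–37% | 86–89% |
| 340 v 170, 70% completion, 63–68% of people all zero* | 5% | 48% | 95% |
| 340 v 170, 70% completion, 30–36% all zero* | 3% | 80% | 100% |
| 340 v 170, 70% completion, 7–10% all zero* | 4–5% | 77% | 100% |
| 340 v 170, 70% completion, mid-scale (latent mean 5) | 4–5% | 4–5% | 7–10% |

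*Share with no shift and with the 0.5-point drop.

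In the three floored 340 v 170 rows, the false SD effect for a 0.5-point drop was −0.06, −0.11 and −0.11 scale points. A further run at 340 v 170 gave 37–46% and 92–97% near the floor, and 4% and 12% mid-scale.

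**Step 3: direction.** Raising the level by 0.5 from the floor raised the SD by 0.12 (81% rejection). Lowering it by 0.5 from near the ceiling raised the SD by 0.11 (87%).

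**Step 4: does adjusting for the mean cure it?** In the setting with 30–36% all zero, adding the baseline and follow-up means left 27% rejection for a 0.5-point drop, and adding the squared follow-up mean left 14%. This adjustment also conditions on a post-randomisation variable.

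**Step 5: relative variability index** (the SD divided by the largest SD possible at that mean). In floored settings it falsely rejected in 10–71% of trials, in the opposite direction. It also dropped 11–66% of participants, because it is undefined for anyone at 0 throughout.

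**The case against.** - **The SD is not primary, and the model is not strictly fixed.** This is correct. Primary Outcomes names mean levels only, and it is an inference, though the natural reading, that the SD goes through the same ANCOVA. The clause allowing another model concerns the distribution of the outcome. A skew-tolerant model of the same raw SD still tests a quantity tied to level.
- **The floor is assumed.** This stands. No EMA distribution is given, and nothing is said about the distribution of the reverse-coded motivation-to-live item. The floor is inferred from the expected skew and from the expectation in Power and Sample Size that 13.9% will report current ideation. The rates move with the assumptions.
- **A reader might infer that any shift in level must appear as reduced variability.** The material does not support that. Mid-scale shifts leave the SD almost unchanged, and some shifts raise it.
- **A reader might also infer that the unequal windows (42 against 21 prompts) bias the comparison.** The schedule is the same in every arm, so it cannot by itself bias a between-arm contrast. The normal-theory small-sample factor at 21 prompts is 0.988, a shortfall of about 1%.
- **The artefact cannot create a benefit from nothing.** This is true: with no shift in level, rejection was 3–6%. What goes wrong is the label put on a real change in level.

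**Conclusion.** The point holds in limited form. As written, the plan appears to test raw within-person SDs of bounded items without regard to level. If scores lie near 0, a pure drop in level can be reported as a drop in variability: false rejection is roughly 30–80% for a 0.5-point latent drop and 85–100% for 1 point. Mid-scale it is 4–5% and 7–12%.

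These figures assume a latent within-person SD of 1.5, 60–70% completion and the latent means used above. They show that the problem can be large; they do not forecast this trial. The confirmatory comparison of mean levels is untouched, and it would be wrong to conclude that the primary result is compromised.

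**What to change.** 1. In the aim 1.1 paragraph of the Analysis Plan, limit the confirmatory ANCOVA to the mean levels of the three indicators named under Primary Outcomes.
2. Label all SD analyses exploratory, at 12 months as well as in the growth models, and state that a raw-SD difference will not be interpreted as a variability effect separate from level.
3. If variability is to be tested, use a mixed-effects location-scale model suited to bounded or censored data, for example with a censored or ordinal likelihood. It keeps participants who score 0 throughout.
4. Use a relative variability index at most as a sensitivity analysis. It excludes all-zero participants after randomisation and over-corrects near the floor.

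The cost is a wording change, modest extra programming, and reliance on the location-scale model's distributional assumption. No data collection changes.
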